| **Outcome(s):** | PRIMARY ENDPOINT  The primary endpoint is the proportion of patients with a pathological PSMA-positive finding (= positivity rate) at one time-point (2h) with the existing standard-of-care (^68^Ga-PSMA-11) compared to the new tracer (^18^F-PSMA-1007).  SECONDARY ENDPOINTS   - Intra-individual comparison of the parametric imaging parameter K*_D_* (measure of tracer affinity) for the two radiotracers. - The number of pathological, benign and uncertain lesions for each tracer in five regions (prostate bed, pelvic lymph nodes, extra-pelvic lymph nodes, bone, or other organs) classified by six blinded readers (three for each tracer) using previously published interpretation guidelines (PSMA-Rads 1.0) - Inter-reader reliability between the three readers for each tracer on the level of the region with respect to three categories (pathological, benign, uncertain). - The region-based positive predictive value (PPV), i.e. the percentage of pathological lesions that are confirmed pathological at the twelve months follow-up (based on the subset of patients and lesions with follow-up data at twelve months). - Tumour visibility will be compared by means of uptake values (SUV) as well as tumour to background contrast in a lesion based analysis. The tumour to background ratio (TBR) is defined as lesion SUV ÷ SUV of reference background region, where the background uptake is defined by convention as the left gluteal musculature. - Number and severity of adverse events per tracer (up to 48h follow up).   OTHER ENDPOINTS OF INTEREST  In a second round of tumour classification, two readers (in consensus) will classify each lesion as pathological, benign or uncertain in a lesion-specific approach and perform a lesion based follow-up to assess PPV on the lesion level. |

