| **Statistical Considerations:** | **Primary Endpoint:**  The primary outcome (proportion of patients with PSMA-positive pathological lesions = patient based sensitivity) will be compared between tracers using an absolute risk difference (new tracer minus old tracer) with a one-sided lower 95% confidence interval for paired proportions (Wald with Bonett–Price Laplace adjustment). If the lower limit lies above -10%, we will claim non-inferiority. Detection rates per patient will be based on majority consensus reads.  **Secondary Endpoints:**   - Parametric imaging will be performed for the two radiotracers in a subset of patients (n=10*), allowing comparison of the tracers’ dosimetric and kinetic parameters, with affinity for the PSMA radioligand by calculation of the parametric equilibrium constant *K*_D,_ which will be compared between the two tracers with descriptive statistics. - The number of PSMA-positive lesions defined as pathological, benign and uncertain per region will be compared using mixed-effects Poisson regression. Patient-level data will also be analysed using the Wilcoxon signed-rank test.. - Inter-reader reliability will be compared on the region level using Krippendorff’s alpha for benign, pathological and uncertain lesions, separately for the two tracers. - Region based PPV will be calculated for each tracer separately with 95% Wilson score confidence intervals. The two tracers will be compared using McNemar’s test and an absolute risk difference with 95% confidence interval. - Semi-quantitative tumour to background ratio (defined as lesion SUV ÷ SUV of reference background region, where the background uptake is defined by convention as the left gluteal musculature) will be summarised on a region-level (i.e. using the mean over all positive lesions per region). Summarised data will be analysed using linear mixed-effects regression models. - The number and severity of adverse event will be analysed using descriptive statistics. All serious adverse events will be listed.   *The requirement for N=10 patients is justified on the previous dosimetry paper for the established PET radiotracer ^68^Ga-PSMA-11 which was adequately powered to demonstrate a mean-effective dose of 0.023 ± 0.004 mSv/MBq, i.e. with a precision in the µSv range [1]. |

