## Secondary Outcomes

- Intra-individual comparison of the parametric imaging parameter K*_D_* (measure of tracer affinity) for the two radiotracers for n=10 patients.
- The number of pathological, benign and uncertain lesions for each tracer in five regions (prostate bed, pelvic lymph nodes, extra-pelvic lymph nodes, bone, or other organs) classified by six blinded readers (three for each tracer) using previously published interpretation guidelines (PSMA-Rads 1.0)
- Inter-reader reliability between the three readers for each tracer on the level of the region with respect to three categories (pathological, benign, uncertain).
- The region-based positive predictive value (PPV), i.e. the percentage of pathological lesions that are confirmed pathological at the 6 month follow-up (based on the subset of patients and lesions with follow-up data at 6 months).
- Tumour visibility will be compared by means of uptake values (SUV) as well as tumour to background contrast in a lesion based analysis. The tumour to background ratio (TBR) is defined as lesion SUV and SUV÷ SUV of reference background region, where the background uptake is defined by convention as the left gluteal musculature.
- Number and severity of adverse events per tracer (up to 48h follow-up, see below)

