## Other Outcomes of Interest

In a second round of tumour classification, two readers (in consensus) will classify each lesion as pathological, benign or uncertain in a lesion-specific approach and perform a lesion based follow-up to assess PPV on the lesion level. This would be impossible to determine using a non-consensus multi-reader approach: lacking a coordinate system for the human body which could unequivocally describe each lesion.

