### Primary Analysis

The primary outcome (proportion of patients with PSMA-positive pathological lesions) will be compared between tracers using an absolute risk difference (new tracer minus old tracer) with a one-sided lower 95% confidence interval (CI) for paired proportions (Wald with Bonett–Price Laplace adjustment). If the lower limit lies above -10%, we will claim non-inferiority. Proportion of pathologic scans will be based on majority consensus reads.

The number of PSMA-positive lesions defined as pathological, benign and uncertain in each region will be analysed using separate mixed-effects Poisson regression models with tracer as fixed covariate and nested random effects for patient and region. We will report incidence rate ratios with 95% CI and p-values. As a sensitivity analysis we will compare the number over all regions using the Wilcoxon signed-rank tests and the Mann-Whitney statistic with 95% CI.

Inter-reader reliability will be analysed on the region-level based on the number of benign, pathological and uncertain lesions determined by each reader. We will calculate Krippendorff’s alpha with a ratio difference function and bootstrap 95% CI separately for each tracer.

Lesion-based PPV will be calculated for each tracer as the proportion of pathological lesions confirmed pathological during follow-up among all lesions with a known state and will be presented with 95% Wilson score CI. Using all lesions with a confirmed status during follow-up, the two tracers will be compared using McNemar’s test and an absolute risk difference with 95% confidence interval.

The semi-quantitative tumour to background ratio will be summarized on a region-level (i.e. using the mean over all positive lesions per region) and analysed using a linear mixed-effects regression model with tracer as fixed covariate and patient and region as nested random effects. The mean difference with 95% CI will be reported.

For the subset of patients with additional parametric imaging data (N=10) the planned analysis of parametric imaging parameters (see first secondary endpoint) is planned prior to completion of the study. This exploratory analysis of this secondary endpoint will not assess the primary endpoint and will not influence further trial conduct or further trial process.

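### Section 11.4.2 analyses a lesion-based PPV where the synopsis and section 5.2 declare a region-based PPV as the secondary endpoint, so the unit and the read are not fixed.

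*Protocol*

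**What the plan says.** The endpoint is stated twice. Section 5.2 lists "The region-based positive predictive value (PPV), i.e. the percentage of pathological lesions that are confirmed pathological at the 6 month follow-up". The synopsis, under Outcome(s), lists "The region-based positive predictive value (PPV), i.e. the percentage of pathological lesions that are confirmed pathological at the twelve months follow-up". Both call it region-based and rank it as secondary, yet both explain it as a percentage of lesions. (They also differ on the follow-up time. That is a separate discrepancy, not pursued here.)

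The analysis is also stated twice. The synopsis, under Statistical Considerations, has "Region based PPV will be calculated for each tracer separately with 95% Wilson score confidence intervals", followed by "The two tracers will be compared using McNemar’s test and an absolute risk difference with 95% confidence interval". Section 11.4.2 has "Lesion-based PPV will be calculated for each tracer", defined as the share of pathological lesions that follow-up confirms, with lesions of known state as the denominator, and then "Using all lesions with a confirmed status during follow-up, the two tracers will be compared using McNemar’s test", again with a risk difference and its 95% interval. Section 11.4.2 contains no region-based PPV and does not say which read supplies the lesions.

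Section 5.3 lists lesion-level PPV as an other outcome of interest, obtained in a second classification round by two readers in consensus. Its comment on obtaining this from independent readers is "This would be impossible to determine using a non-consensus multi-reader approach". Section 9.2.3 repeats the reason: there is no coordinate system by which several readers could refer to the same lesion.

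**The concern.** A region and a lesion are different units of analysis. With regions, a patient contributes at most five units per tracer. With lesions, a patient with many metastases contributes as many units as there are lesions and can dominate the estimate.

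The read changes with the unit. The protocol's own argument is that independent readers cannot supply lesion-level PPV, so an analyst who follows section 11.4.2 has to use the consensus round. The secondary endpoint would then be filled by an outcome that the protocol ranks below it.

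Follow-up confirmation comes from an unmasked review of records (section 6.1.2.2, item 7). If both texts remain in force at that stage, the unit can be chosen with the results in view.

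**Working it through.** The plan states no figure for PPV, so there is none to reproduce. The 85% power in section 11.2 concerns the primary endpoint only and has no bearing here. The check is a comparison of the texts, followed by an illustration of size.

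**Texts side by side**

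| Place | Rank | Unit named | Read named |
| --- | --- | --- | --- |
| Synopsis, Outcome(s) | Secondary | Region, explained by counting lesions | None |
| Section 5.2 | Secondary | Region, explained by counting lesions | None |
| Synopsis, Statistical Considerations | Secondary | Region | None |
| Section 11.4.2 | Not stated | Lesion | None |
| Sections 5.3 and 9.2.3 | Other outcome | Lesion | Two readers in consensus, second round |

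1. Section 11.4.2 and the synopsis use the same three tools: Wilson intervals, McNemar's test and a risk difference. Only the unit differs.
2. After the primary outcome, section 11.4.2 takes lesion counts, reader reliability, PPV and tumour-to-background ratio in the order of section 5.2. Its PPV paragraph stands where the secondary endpoint belongs and mentions neither a second round nor a consensus.
3. Section 6.1.2.2, item 5, has the independent readers record numbers of lesions by type and by region. Lesions are not individually identified. McNemar's test on lesions needs the same lesion matched across both scans, and counts per region cannot provide that match. This agrees with section 5.3.
4. So if the PPV paragraph of section 11.4.2 is meant for the secondary endpoint, its unit is wrong. If it is meant for the section 5.3 outcome, it does not say so, and section 11.4.2 then leaves out the declared secondary PPV. Either way the text needs correcting.

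**Illustration of size (all inputs assumed)**

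Take 60 positive regions with one lesion each, of which 42 (70%) are confirmed. Add 10 patients, each with one bone region holding m lesions. A share q of those 10 regions is confirmed, and all lesions within a region share its status.

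- Region PPV = (42 + 10q) / 70
- Lesion PPV = (42 + 10mq) / (60 + 10m)

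| m | q | Region PPV | Lesion PPV | Lesion minus region |
| --- | --- | --- | --- | --- |
| 1 | 1.0 | 52/70 = 74.3% | 52/70 = 74.3% | 0 |
| 3 | 1.0 | 52/70 = 74.3% | 72/90 = 80.0% | +5.7 points |
| 10 | 1.0 | 52/70 = 74.3% | 142/160 = 88.8% | +14.5 points |
| 10 | 0.7 | 49/70 = 70.0% | 112/160 = 70.0% | 0 |
| 10 | 0.4 | 46/70 = 65.7% | 82/160 = 51.3% | −14.5 points |

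The gap vanishes when every region has one lesion (m = 1) or when confirmation is equal in both kinds of region (q = 0.7). It changes sign when multi-lesion regions are confirmed less often.

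The rule for confirming a region matters too. Suppose 7 of the 10 lesions in each bone region are confirmed, and one confirmed lesion is enough to confirm the region. Region PPV is then (42 + 10)/70 = 74.3%, while lesion PPV is (42 + 70)/160 = 70.0%.

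**The case against.** A reader might infer three stronger things that the documents do not support.

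- **That the declared endpoint has no analysis at all.** The synopsis gives a complete region-based one. The defect is a contradiction between the synopsis and section 11.4.2.
- **That the protocol assigns the secondary PPV to the six-reader read.** The PPV entries name no readers. Section 5.2 names the six readers for the lesion counts, and the three per tracer for reliability. The link to PPV is a fair inference from the shared regions, but it is not stated.
- **That the consensus round uses different people.** Sections 5.3 and 9.2.3 say only that there are two readers.

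The best defence is that the intended unit was never purely regional. The explanation attached to the endpoint counts lesions, and section 11.4.2 nearly repeats it. Section 6.1.2.2 (item 7) and section 6.1.3 describe lesion-based accuracy from follow-up, and section 9.2.2 speaks of follow-up for lesions rated pathological. This stands, but it widens the ambiguity: the correction has to reach the endpoint wording as well as section 11.4.2.

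It is also fair that the consequence is limited. Section 9.2.2 calls the outcome explorative, and confirmation exists only where routine care produces it. The endpoint has no power calculation and does not touch the primary non-inferiority conclusion. The illustration is constructed, and it says nothing about the difference between tracers, which the documents give no basis for calculating.

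A separate statistical analysis plan would not remove the problem, because its author would first have to decide which protocol text to depart from.

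**Conclusion.** The point holds as a contradiction in unit, and consequently in read, for a declared secondary endpoint. It should be corrected, but it does not threaten the primary analysis.

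The finding itself rests on the protocol's wording and on no assumed figure. Its numerical effect cannot be derived from the documents. It depends on how lesions cluster within regions, on whether confirmation differs in multi-lesion regions, and on the rule for confirming a region. Under the assumed structure above, lesion PPV ranges from 14.5 points below region PPV to 14.5 points above it, and the two coincide in the cases noted. The upper end is the scenario of 74% against 89%.

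**What to change.** 1. In section 11.4.2, make the secondary PPV region-based and name the read it uses. One option is to call a region positive when at least two of the three readers for that tracer rate it pathological. This extends the majority rule that section 6.1.2.2 gives for the scan as a whole, so it has to be written down as a new rule.
2. State when a region counts as confirmed, in particular when only some of its lesions are confirmed. Use positive regions with known status as the denominator.
3. Edit the explanation of the endpoint in the synopsis and in section 5.2 so that it counts regions.
4. Label lesion-level PPV from the consensus round as the exploratory analysis of the section 5.3 outcome, reported separately. Align the follow-up wording in sections 6.1.2.2, 6.1.3 and 9.2.2 with this split.

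The cost is a few sentences and one decision, the confirmation rule, to be taken before the follow-up results are examined. No new reads are needed.

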## Secondary Objectives

Secondary objectives are

- to provide a head-to-head comparison of tracer kinetics

- to compare the number of pathological, benign and uncertain lesions found with the two tracers

- to determine the intra-reader agreement for the two tracers

- to compare the proportion of pathological lesions confirmed in a follow-up between the two racers

- to compare tumour visibility between the two tracers

- to evaluate safety and tolerability for the two tracers

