### Response Criteria

Response to targeted treatment (surgery, radiotherapy) will be considered as confirmatory in the case of a fall in PSA, using previously published response criteria [22]. Where PET scan findings are recorded as positive, but the follow up refutes this, the scan will be recorded as false positive. Established RECIST (Vers 1.1) criteria will be used to interpret correlative imaging [23]. The details are as follows:

Follow up of clinical notes to 6 months will be performed for histopathological data, additional conventional imaging (CT, MRI and or bone scintigraphy), PSA change following focal salvage therapy (where no systemic therapy has been applied. Follow-up imaging will be performed by local read.

1. **Follow up histology**

Positive biopsy or histology will be taken to be confirmatory.

For negative biopsies: to rule out false negative imaging for image-guided biopsy will be reviewed. For lymph node biopsies, comparison of the PET/CT and follow-up (post intervention) imaging will be made to confirm that biopsy of the correct node occurred.

1. **Follow up imaging**

No established imaging criteria are available for a number of imaging modalities in recurrent prostate cancer. To enable comparison of these data with previous imaging trials, the imaging criteria as previously published by Fendler et al. will be used (§2.1.5.3 of Supplementary Materials 2: Trial Protocol [24])

1. **Follow up following local treatment**:

PSA change following radiation therapy will be according to previously published criteria, with a PSA response of > 50% taken to be confirmatory [25] (see figure 4).

[figure not shown]

**Fig.4.** Example interpretation criteria for patients undergoing biopsy or radiotherapy (with and without systemic hormone deprivation therapy) image from Emmett et al. [25]

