### Assessment of secondary outcomes

Tumour to background ratio will be compared for both tracers, as described previously in this protocol.

Confirmation for lesions will only be available where the patient’s condition dictates further clinical follow up, such as repeat imaging, or where histology is performed. This data will be collected, and as a secondary explorative outcome, follow-up for lesions rated as pathological will be done by composite follow-up standard of imaging, PSA and histology up to 6 months’ follow up. It is important to note that the performance of histology, further imaging or treatment is not a study specific intervention and is performed when considered clinically appropriate by the patient’s treating physician.

For n=10 individuals parametric imaging will be performed using standard parametric imaging analysis software with only descriptive statistics.

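### The PPV and its tracer comparison rest only on lesions that routine care happened to verify, so both can be biased if verification is related to true lesion status

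*Protocol*

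**What the plan says.** The relevant objective in section 4.3 is "to compare the proportion of pathological lesions confirmed in a follow-up between the two" tracers. Section 5.2 turns this into a region-based PPV that is "based on the subset of patients and lesions with follow-up data at 6 months"; the synopsis states the same restriction, but at twelve months. Section 11.4.2 sets the denominator, here per lesion, by defining PPV as "the proportion of pathological lesions confirmed pathological during follow-up among all lesions with a known state". It adds Wilson intervals, McNemar's test and a risk difference with a 95% interval.

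On how a lesion gets a known state, section 9.2.2 says: "Confirmation for lesions will only be available where the patient’s condition dictates further clinical follow up", or where histology is done. It adds that "the performance of histology, further imaging or treatment is not a study specific intervention" and that these steps are left to the treating physician. Section 3.7.2 says that the clinical reports of all scans go to that physician. Section 11.5, on missing data, covers loss to follow-up and withdrawal but not lesions that nobody verified.

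**The concern.** The physician who decides whether to pursue a lesion has seen a report of the scan being evaluated. A lesion that looks convincing may be biopsied, re-imaged or treated, while one that looks doubtful may be left alone and drop out of the PPV. Under section 6.1.4 a positive scan counts as false positive only where follow-up refutes it, so an untouched lesion never counts against a tracer. The same section limits the PSA route to patients without systemic therapy, which may remove other lesions, possibly true ones. Selection could therefore act in either direction, and a verified-only PPV does not show which.

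The primary endpoint counts positive calls without a reference standard, so the PPV results are the trial's only check on whether additional positive calls are real. Section 3.4 reports more non-prostatic uptake with the new tracer, which makes the check relevant and makes it plausible that verification differs by tracer.

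**Working it through.** **The plan's own figures.** The protocol states no expected PPV, verified fraction or power for this endpoint. Its only power figure is 85% for the primary comparison (section 11.2). That figure reproduces at 86.5% by simulation with the Bonett–Price limit at one-sided 2.5%, and nothing below affects it. **All PPVs and verification rates that follow are assumptions.**

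**Formula.** Let P be the true PPV, and let vT and vF be the probabilities that a truly and a falsely pathological lesion is verified. Then

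observed PPV = P·vT / [P·vT + (1−P)·vF].

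**1. Verification unrelated to status (vT = vF).** The rates cancel and observed PPV = P. This holds even if one tracer's lesions are verified at 40% and the other's at 60%. Bias: 0.

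**2. Related to status, equally for both tracers (vT 60%, vF 30%).**
- P = 80%: 0.48/(0.48+0.06) = 88.9%.
- P = 70%: 0.42/(0.42+0.09) = 82.4%.
- Equal true PPVs give an observed difference of 0. A true difference of −10 points (70% v 80%) is seen as −6.5. The sign is kept and the size shrinks.

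**3. Related to status, differently by tracer (vT 60% for both; vF 60% for the old tracer, 20–30% for the new).**

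| True PPV, new v old | vF new | Observed new | Observed old | Observed difference |
|---|---|---|---|---|
| 80% v 80% | 30% | 88.9% | 80% | +8.9 |
| 80% v 80% | 20% | 0.48/0.52 = 92.3% | 80% | +12.3 |
| 70% v 80% | 30% | 82.4% | 80% | +2.4 |
| 70% v 80% | 20% | 0.42/0.48 = 87.5% | 80% | +7.5 |

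In the last two rows a true deficit of 10 points appears as an advantage. With the pattern reversed (new vF 60%, old vF 30%), a true difference of 0 appears as −8.9.

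**4. How demanding is case 3?** A lesion called on both tracers has a single verification outcome, so a gap in vF must come mainly through discordant lesions. Suppose a share s of the new tracer's false positives is shared with the old tracer and verified at 60%, and the remainder is never verified. Then vF(new) = 0.6s. A value of 30% needs s = 0.5, and 20% needs s = 1/3. So half to two thirds of the new tracer's false positives would have to be seen on that tracer alone and never pursued. This is possible but towards the strong end.

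**5. Bounds without any model.** With verified share v and confirmed share c among the verified, the lower bound is c·v (no unverified lesion is true) and the upper bound is c·v + (1−v) (all are).
- v = 60%, c = 90%: 54% to 94%.
- c = 80%: 24–94% if v = 30%, 40–90% if v = 50%, 56–86% if v = 70%.

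**6. All pathological calls as the denominator.** This estimates P·vT, not P. With equal PPVs of 80% and status-independent verification of 40% v 60%, it gives 32% v 48%, a spurious −16 points. The planned verified-only PPV is unbiased in that case.

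**The case against.** The strongest reply is that the protocol hides nothing. Section 5.2 and the synopsis declare the subset, section 9.2.2 calls the outcome explorative, and sections 6.1.2 and 6.1.3 speak of descriptive analysis where data are available. Without study-mandated verification, some incompleteness is unavoidable. This stands: a reader might infer that 11.4.2 contradicts the objective in 4.3, but the endpoint definition openly narrows the objective to lesions with follow-up.

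A reader might also infer that the tracer comparison is biased as a matter of fact. The documents do not support that. Bias requires verification to depend on true status among lesions already called pathological, and no rate is given from which to judge this. Several features weaken the mechanism. Readers have an uncertain category, which should take many doubtful lesions out of the PPV. The clinical reports come from physicians outside the trial, so the treating physician acts on a different read from the one that defines PPV. Lesions seen on both tracers share one outcome. The direction is open too: section 3.4 says that uncertain lesions can prompt extra testing, and the systemic-therapy restriction closes only the PSA route, leaving histology and imaging.

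Finally, a statistical analysis plan may contain bounds or a table of unverified lesions, so their absence from the protocol is not itself a fault. What the reply does not answer is that section 11.4.2 fixes a formal test and confidence interval on this subset, without making their interpretation conditional on verification.

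**Conclusion.** The point holds as a risk. The verified-only PPV is unbiased if verification is unrelated to true status. It is biased, with any non-zero tracer difference rescaled, if verification depends on status equally for both tracers. The tracer difference can be created or reversed if the dependence differs by tracer. Under the assumed rates, the bias in the difference runs from 0 to +17.5 points (true −10 seen as +7.5), or −8.9 with the pattern reversed. The larger values need many discordant, unpursued false positives. With 60% verified and 90% of those confirmed, the data would be compatible with a PPV of 54% to 94%. This is a limitation of a declared, explorative secondary endpoint; the non-inferiority conclusion does not depend on it.

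**What to change.** In section 11.4.2 and the synopsis:

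- Keep the verified-only PPV and label it as PPV among verified lesions or regions. Use one unit throughout, since sections 5.2 and 11.4.2 differ, and reconcile the six- and twelve-month follow-up statements, because follow-up length affects how many lesions are verified.
- Report the numbers confirmed, refuted and unverified for each tracer.
- Add a sensitivity analysis with lower and upper bounds for each tracer, counting all unverified calls first as not confirmed and then as confirmed.
- State that McNemar's test and the risk difference are descriptive and conditional on verification.

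Do not make all pathological calls the denominator of the main PPV: that mixes PPV with the verification rate (step 6). The proportion confirmed among all calls belongs in the table as the lower bound.

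The cost is a wording change and one more table from data already collected. The downside is that the PPV is shown with a wider and less favourable range.

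### McNemar's test does not compare the two tracers' positive predictive values, the Wilson intervals ignore clustering within patients, and the unit (lesion or region) is not settled

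*Protocol*

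**What the plan says.** Section 11.4.2 (Primary Analysis) defines the per-tracer estimate: "Lesion-based PPV will be calculated for each tracer as the proportion of pathological lesions confirmed pathological during follow-up among all lesions with a known state". It adds that this "will be presented with 95% Wilson score CI". The comparison follows: "Using all lesions with a confirmed status during follow-up, the two tracers will be compared using McNemar’s test", together with an absolute risk difference and its 95% interval.

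The synopsis (Statistical Considerations) names the same two methods for another unit: "Region based PPV will be calculated for each tracer separately with 95% Wilson score confidence intervals". Section 5.2 also defines the endpoint by region: "The region-based positive predictive value (PPV), i.e. the percentage of pathological lesions that are confirmed pathological at the 6 month follow-up". Section 5.3 says of PPV at lesion level, which it assigns to a two-reader consensus round: "This would be impossible to determine using a non-consensus multi-reader approach".

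Section 9.2.2 gives the status of the endpoint: "as a secondary explorative outcome, follow-up for lesions rated as pathological will be done by composite follow-up standard".

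No adjustment for several lesions or regions per patient is stated for PPV. In the same section, the lesion-count and tumour-to-background models both carry nested random effects for patient and region.

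**The concern.** PPV asks how often a positive call is right. Each tracer is judged on its own positive calls, and these sets overlap only in part. McNemar's test needs one common set of units rated by both tracers, and it uses only the discordant pairs. A lesion positive on both tracers has one true status, so both calls are right or both are wrong, and it adds no discordant pair for correctness. What remains is driven largely by which tracer calls more lesions.

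This matters because the primary endpoint counts any pathological call, true or false, and PPV is the comparison tied to a reference standard. Section 3.4 reports more non-prostatic uptake with the new tracer and regards that as clinically relevant, so unequal yield is plausible. A p-value that answers a question about yield would then be reported as an answer about PPV.

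The intervals raise a second issue. Lesions in one patient share disease and treatment. Under section 6.1.4 a fall in PSA after local treatment can count as confirmation, and that is a patient-level result shared by all the lesions treated.

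**Working it through.** **The plan's own figure.** None is given for the PPV comparison. The only power figure (85%, section 11.2) concerns the primary endpoint and does not enter here.

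**Notation.** Among verified lesions positive on at least one tracer, let t be confirmed and f refuted, with subscripts *both*, *A* (A only) and *B* (B only).

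PPV_A = (t_both + t_A) / (t_both + t_A + f_both + f_A), and likewise for B.

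McNemar uses only two discordant counts. The text does not define the table, so three readings are possible:

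1. Positive call: t_A + f_A against t_B + f_B
2. Confirmed lesions only: t_A against t_B
3. Correct classification: t_A + f_B against t_B + f_A

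Equality in any of these neither implies PPV_A = PPV_B nor follows from it.

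**Equal PPV, unequal yield (assumed scenario).** Take 150 verified lesions, 60% seen by both tracers, 10% by A only and 30% by B only, each confirmed with probability 0.8. The expected counts are 90, 15 and 45.

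- PPV_A = (72 + 12)/105 = 80%; PPV_B = (72 + 36)/135 = 80%.
- Reading 1: 15 v 45, chi-square 30²/60 = 15.0
- Reading 2: 12 v 36, chi-square 24²/48 = 12.0
- Reading 3: 12 + 9 = 21 v 36 + 3 = 39, chi-square 18²/60 = 5.4

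All three exceed the 5% critical value of 3.84 although the PPVs are equal. In 4,000 simulated trials the rejection rates were 98%, 95% and 65%; a repeat gave 97%, 93% and 63%. Exact p-values lower the third rate by a few more points. A test of the PPV difference that allows for the pairing rejected in 4.8%. With equal yield (20% and 20%) all the tests were near 5%, so the fault appears when yields differ.

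**The sign can be wrong (constructed table).** Confirmed: 60 both, 4 A only, 36 B only. Refuted: 6 both, 2 A only, 16 B only.

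- PPV_A = 64/72 = 88.9%; PPV_B = 96/118 = 81.4%.
- Difference 7.5 points in favour of A (95% CI 0.3 to 14.7, p = 0.040, lesions treated as independent).
- McNemar favours B on every reading: 6 v 52 (p < 0.001), 4 v 36 (p < 0.001), 20 v 38 (p = 0.025).

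**Wilson coverage.** The protocol gives neither the number of lesions per patient nor the intra-patient correlation (ICC). Assumed: 50 patients with verified lesions, PPV 0.8, beta-binomial clustering. The design effect with m lesions per patient is 1 + (m − 1) × ICC.

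| Lesions per patient | ICC | Design effect | Coverage, fixed counts | Coverage, skewed counts, same mean |
|---|---|---|---|---|
| 2 | 0.1 | 1.1 | 93% | 93% |
| 2 | 0.3 | 1.3 | 90% | 88% |
| 3 | 0.3 | 1.6 | 88% | 82% |
| 4 | 0.3 | 1.9 | 86% | about 76 to 77% |

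**The unit.** Section 11.4.2 analyses lesions; the synopsis and section 5.2 define the endpoint by region. The six-reader reads give counts per region, and section 5.3 says they cannot yield lesion-level PPV. The lesion-by-lesion pairing that McNemar needs therefore exists only in the consensus round. At region level it can be formed, but regions positive on one tracer only raise the same problem and regions are still clustered in patients.

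**The case against.** The best defence is that the endpoint is explorative, that verification comes only from routine care, and that sections 6.1.2 and 6.1.3 call the lesion-based accuracy analysis descriptive. Each tracer's PPV is also reported separately, so a gap would be visible beside any p-value. This stands, and it limits the severity.

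Four stronger readings are tempting, and the documents do not support them.

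- *As written, the tracer that calls more lesions wins, including when the extra calls are false.* That depends on the table chosen. Take confirmed 100 both, 20 new only, 14 old only, and refuted 4 both, 26 new only, 2 old only. PPV is 120/150 = 80% for the new tracer and 114/120 = 95% for the old. Positive calls favour the new tracer (46 v 16, p = 0.0002), confirmed lesions favour neither (20 v 14, p = 0.39), and correct classification favours the old (22 v 40, p = 0.03). Section 9.2.3 refers benign and equivocal lesions to follow-up too, which makes the last reading plausible. A reversal can occur, but it is not built in.
- *The risk difference has the same fault.* The text does not call it paired. It may be meant as the difference of the two PPVs; it is only undefined.
- *PPV is the only check on false positives.* Benign and uncertain lesion counts are compared as well, and refuted scans are recorded as false positive (section 6.1.4).
- *Lesion-level PPV is impossible in this trial.* Section 5.3 says so of the multi-reader reads, to explain why the consensus round exists. That accounts for part of the unit conflict; the mismatch between section 11.4.2 and the synopsis remains.

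**Conclusion.** The point holds. The stated test does not address equality of PPV under any reading of its table. The 63 to 98% rejection rate rests on an assumed difference in yield, and the sign reversal rests on a constructed table; the protocol has no data to say how likely either is. The Wilson intervals are too narrow whenever lesions or regions within a patient are positively correlated. The loss ranges from about 2 points of coverage (ICC 0.1) to about 9 points (ICC 0.3, four lesions each), and about 18 points if lesion counts are strongly skewed, all on assumed inputs. The unit must be reconciled whichever test is used.

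This should be fixed, but it does not threaten the trial. A reader might infer that the main conclusion is at risk; it is not, because the primary comparison and the 100 patients do not depend on PPV.

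**What to change.** In the synopsis and section 11.4.2:

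1. Make the patient-by-region majority call the unit for the secondary PPV, and keep lesion-level PPV for the two-reader consensus round.
2. Compare PPV with a marginal (GEE) model of confirmed status on tracer among tracer-positive units with known status, clustered by patient, or with a weighted generalised score test clustered in the same way.
3. Define the absolute risk difference as the difference of the two PPVs.
4. Take the interval for each PPV and for their difference from that model or from a patient-level bootstrap.
5. If McNemar's test is kept, relabel it as paired detection among confirmed regions.

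The cost is a change of wording and a little code. No new data are needed. The intervals will be somewhat wider.
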